### Process evaluation

The process evaluation has three aims: to examine the feasibility of implementing the intervention, to understand the mechanisms through which change occurred and to consider the role of context in shaping this change [45]. In keeping with the MRC guidelines, we will use quantitative and qualitative methods to address these aims.

#### Feasibility of intervention implementation

We aim to understand and document the key lessons learned from implementing SOLID (both the interventions and the trial processes) and to evaluate factors needed to deliver the intervention at scale. With regard to the intervention delivery, we will use Carroll et al.’s definition of fidelity, i.e. we will assess whether intervention sessions are delivered as planned in terms of content, frequency, duration and coverage [46]. We propose to assess the quality of intervention delivery (treatment fidelity) by applying a validated process rating scale (UKATT PRS) [47], developed in the UKATT trial. All sessions will be audio recorded, and a 20% random sample of SBNT and MET sessions will be analysed, ensuring we sample early, mid and late sessions of both interventions. UKATT PRS specifically covers MET and SBNT and assesses items including commitment, optimism, collaboration and interpersonal focus, which help determine if the LAC are actively engaged in the intervention sessions.

#### Mechanism of change

Interview schedules for staff (drug and alcohol workers and social workers) will be constructed to highlight the four core concepts of the Normalisation Process Theory [48]: coherence, cognitive participation, collective action and reflexive monitoring. Qualitative data will be collected through interviews and focus groups with social workers and drug and alcohol workers. Data collection will continue until saturation; however, as a minimum, we will carry out qualitative semi-structured interviews with 15 drug and alcohol workers and two focus groups, one with social workers and one with members from the drug and alcohol teams. The workers will be purposefully sampled to ensure that there are professionals interviewed from each local authority site and each intervention arm. The analysis will inform our understanding of the mechanism of change from a practitioner perspective and consider key barriers to successful delivery and integration of the interventions at the level of the system.

We will conduct a minimum of 20 qualitative 1:1 semi-structured interviews with a purposive sample of LAC (ensuring maximum diversity with regard to gender, placement type, study arm and age) and separate interviews with their carers (*n* = 20). These interviews aim to understand how the interventions have affected the LAC themselves and how they would recommend changing the interventions to make them more effective.

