### Aim

The SOLID pilot feasibility trial (Supporting Looked After Children and Care Leavers In Decreasing Drugs, and alcohol) aims to investigate whether it is possible to recruit and retain, to 12-month follow-up, LAC aged 12–20 years, who screen positive for drug and/or alcohol use, into a randomised controlled trial of behaviour change interventions to reduce risky substance use (illicit drugs and alcohol) and improve mental health.

The specific objectives of the pilot feasibility trial are:To establish response rates, variability of scores, data quality and acceptability of the proposed outcome measures for self-reported alcohol and drug use, health-related quality of life, mental health and well-being, sexual behaviour and placement stability 12 months post-baseline, in order to design a definitive multi-centre RCTTo assess engagement and participation with the adapted Motivational Enhancement Therapy and Social Behaviour and Network Therapy based interventions by LAC, their support network and frontline drug and alcohol workersTo assess the fidelity of intervention delivery by drug and alcohol workers and pilot a tool for measuring fidelity of the adapted interventionsTo develop cost assessment tools, assess intervention delivery costs and carry out a value of information analysis to inform a definitive studyTo apply pre-specified ‘stop/go criteria’ and determine if a definitive multi-centre randomised controlled trial is feasible and, if so, develop a full trial protocol

Clear success (‘go’) criteria for this feasibility trial would be for at least 60% of eligible participants to consent to taking part in the trial, to successfully recruit 50 LAC per arm and retain at least 70% of participants at 12-month follow-up. In addition, data from interviews and focus groups should indicate whether trial processes are acceptable to staff and LAC. The individual interventions will be assessed as feasible if the intervention can be delivered with fidelity and at least 80% of the participants attend 60% of the intervention sessions.

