#### Qualitative analysis

Data transcription will be carried out verbatim. Transcripts will be anonymised by removing names of any individuals mentioned in the course of the interview; a participant key will be stored separately. Transcripts will be subject to thematic analysis [49]; analysis will be an iterative process, using the constant comparative method [50], derived from grounded theory. Qualitative software (NVIVO 10) will aid in the organisation of thematic codes and categories.

As described above, the qualitative process evaluation will provide rich data on the feasibility of the interventions and on the ‘mechanisms of change’ and the role of context. This will include data on fidelity (assessment of content and interaction), acceptability (LAC and practitioner perceptions about receiving and delivering the actual interventions) and the potential ‘mechanism of change’ (whether our theory of change pathways are borne out in practice) from both the perspective of the service provider and LAC (service user). These data will allow us to assess if either of the interventions is clearly more acceptable to both service users and providers, is more likely to be integrated into routine service delivery, and has greater potential to elicit behaviour change in the young person. The data collected within the qualitative interviews and focus group will be used to draw elements of the MET and SBNT interventions together into a single ‘optimised’ intervention if appropriate. This may occur if core components of each intervention are consistently reported as being acceptable to LAC and practitioners and can be combined together in a complementary way whilst retaining the essence of each approach.

Qualitative and quantitative data will be collected simultaneously, and both sources of data will be analysed separately; however, the data from different methods will be triangulated to ‘consider where findings from each method agree (convergence), offer complementary information on the same issue (complementarity) or appear to contradict each other (discrepancy or dissonance)’ [51].

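### The interview sample of young people is not spread over engagement, so low attenders and withdrawers may be under-represented in the acceptability evidence

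*Protocol article*

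**What the plan says.** The section Mechanism of change fixes the number and type of interviews with young people: "We will conduct a minimum of 20 qualitative 1:1 semi-structured interviews with a purposive sample of LAC". It then names the dimensions of the sample: "ensuring maximum diversity with regard to gender, placement type, study arm and age". Attendance, stopping sessions and withdrawal are not among them, and no other section adds them. The purpose given there is about the interventions: "These interviews aim to understand how the interventions have affected the LAC themselves", together with how the young people would change them.

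Two other places rely on these data. After the numerical success criteria, the Aim section adds that "data from interviews and focus groups should indicate whether trial processes are acceptable to staff and LAC". The Qualitative analysis section says that the data will be used to "assess if either of the interventions is clearly more acceptable to both service users and providers", and possibly to merge parts of both interventions into one.

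The Aim section also sets numerical criteria for consent ("at least 60% of eligible participants to consent to taking part in the trial"), for retention ("retain at least 70% of participants at 12-month follow-up") and, for each intervention, for attendance ("at least 80% of the participants attend 60% of the intervention sessions").

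**The concern.** How far a young person engaged is probably the characteristic most closely tied to whether he or she found the intervention or the trial acceptable. A purposive sample can be well spread over gender, placement, arm and age and still consist mainly of people who kept attending, because they are the easiest to reach. Such a sample would tend to report higher acceptability than the full group of participants would.

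Two uses of the data are at stake. One is the judgement that trial processes are acceptable. The other is the comparison of MET with SBNT, including the choice of components for a combined intervention. Attendance and retention rates will show how many young people left. They will not show whether the intervention, the trial procedures or something unrelated, such as a placement move, was the reason. A definitive trial needs that information, and the people who can give it are those whom the sampling list does not secure.

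**Working it through.** **Other sources of the missing views.** Set beside the sampling list, the article's other sources do not replace it:

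- Carer interviews (Mechanism of change) are with the carers of the interviewed young people, on the natural reading, so they carry the same selection.
- Session recordings (Feasibility of intervention implementation) exist only for sessions that took place. Someone who never attends leaves none.
- The description of non-completers (Statistical analysis) is quantitative. It shows who left, not why.
- Interviews and focus groups with practitioners and social workers give staff views. They can report on young people who left, but at second hand.

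**Inputs.** The article states no expected number of disengaged interviewees, so there is no figure of its own to reproduce on this point.

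- n = 20 interviews, the stated minimum (Mechanism of change).
- q = share of low attenders. The attendance criterion (Aim) is met when at least 80% attend enough sessions, so it tolerates q up to 1 − 0.80 = 0.20.
- r = chance that a low attender is interviewed, relative to another participant. The article does not give this. It is an assumption, shown over a range.

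**Formula.** The share of low attenders among interviewees is s = qr / (qr + 1 − q), and the expected number is 20s. As a rough guide, the chance of at most one is (1 − s)^20 + 20s(1 − s)^19. The binomial is only an approximation, because selection is purposive.

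**Results with q = 0.20.**

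| r | s | Expected of 20 | Chance of at most one |
|---|---|---|---|
| 1 | 0.20/1.00 = 0.200 | 4.0 | 6.9% |
| 0.5 | 0.10/0.90 = 0.111 | 2.2 | 33% |
| 0.25 | 0.05/0.85 = 0.059 | 1.2 | 67% |

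**Control interviewees.** The table applies q to all 20. Control participants have no MET or SBNT sessions to miss, and study arm is one of the sampling dimensions. If the 20 were split evenly over three arms (an assumption), about 13 would come from MET and SBNT together. The expected numbers of low attenders then fall to 13 × 0.200 = 2.6, 13 × 0.111 = 1.4 and 13 × 0.059 = 0.8 over both interventions.

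**Possible overstatement, with invented rates.** Suppose 90% of engaged and 40% of low-attending participants find an intervention acceptable. The true figure is 0.80 × 0.90 + 0.20 × 0.40 = 80%. Interviews would show 0.889 × 0.90 + 0.111 × 0.40 = 84% at r = 0.5, and 0.941 × 0.90 + 0.059 × 0.40 = 87% at r = 0.25. The direction follows from the selection. The amount depends wholly on the assumed rates.

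**The case against.** The strongest reply is that the go decision does not hang on these interviews. A reader might infer that acceptability by itself decides go or stop. The Aim section does not say so: the interview evidence is an addition, without a threshold, to numerical criteria for consent, recruitment and retention, and each intervention is judged separately on fidelity and attendance. If more than 30% are lost, or more than 20% attend too little, a numerical criterion fails whatever the interviewees say. This stands, and it limits the consequence. The go consideration also concerns trial processes. Acceptability of the interventions enters through the Qualitative analysis section, where the views of providers count too.

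A reader might also take the 30% loss to follow-up as the share of disengaged young people and conclude that 0.30 × 20 = 6 interviewees ought to come from that group. The article does not support this. The 30% is an allowance for missing 12-month data in all three arms, and a person lost at 12 months may have attended every session. The figure that bears on sessions is the 20% tolerance, which gives 4 of 20.

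Nor do the documents show that disengaged participants will be nearly absent. That would require them to be much harder to interview, and the article is silent on this. Twenty is a minimum, non-attenders are not excluded, and if they are as easy to interview as others, a sample with at most one is unlikely (6.9%).

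Finally, the article condenses a fuller protocol. That reply is weak here, because the sampling dimensions are listed explicitly.

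**Conclusion.** The point holds as a modest, inexpensive improvement to the design. The listed sampling dimensions omit engagement, the interviews are used to judge acceptability, and no other source secures the first-hand views of low attenders and withdrawers. Their under-representation, and an overstatement of acceptability, is a possibility that the plan does not guard against, not a demonstrated result.

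At the tolerated 20% of low attenders, the expected number among 20 interviewees runs from 4.0 (equally likely to be interviewed) through 2.2 (half as likely) to 1.2 (a quarter as likely). It is lower if some of the 20 are controls. These figures rest on the assumed relative chance of interview. They also treat all low attenders as disengaged, although the intervention sections allow MET and SBNT to finish in fewer than six sessions where that suits the young person. The effect on the go decision is limited by the numerical criteria. The effect on understanding why young people leave, and on the comparison of MET with SBNT, is more direct.

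**What to change.** In Mechanism of change, add engagement status to the sampling dimensions for the interviews with young people, within the same 20 interviews. Three categories are enough: completed, including completion in fewer sessions by agreement; stopped attending or never attended; withdrew from the trial.

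Set a small minimum of disengaged participants from each of MET and SBNT, for example two per arm, which makes 4 of 20. If the attendance criterion is only just met, 20% of 50 gives up to 10 low attenders per arm from whom to draw them.

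Do not define the group by attendance below 60% alone. A young person who finishes by agreement in three of six sessions has attended 50% and would be wrongly counted as disengaged.

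In Qualitative analysis, state that acceptability will be reported by engagement status, both for trial processes and for each intervention.

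The change takes a few sentences and no extra interviews. The downside is more contact attempts per interview, and withdrawn participants can be approached only where their consent allows it.

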#### Context

The role of context will be core to our understanding of the mechanism of change at the level of the service user (LAC) and service provider (drug and alcohol workers and social workers). Specifically, we will consider barriers and facilitators to change.

### Planned analysis

#### Statistical analysis

As a pilot feasibility trial, the main analyses will be descriptive, in order to inform the design of a future definitive study. The primary outcomes are feasibility outcomes. We will report the numbers of eligible participants seen over the recruitment period and the resulting rates of recruitment, compliance with randomisation and data completion. Non-completers will be characterised. In addition, the descriptive analysis will include participant characteristics (for example age, gender, ethnicity, substance use type, mental health and well-being, sexual health).

The pilot feasibility trial will also assess performance of potential outcome measures for a definitive trial. We will ascertain data completeness of the instruments and any potential bias in the completion of follow-up data to inform the choice of instruments in a future trial. The majority of the outcome data will be presented in simple descriptive tables presenting percentages, means and standard deviations or 5-number summary (as appropriate), for each arm of the study. We will use an intention to treat analysis. This information will be used to inform the design, choice of primary outcome, necessary sample size and approach to the analysis, of the future definitive trial.

#### Health economic analysis

The initial stage of value of information (VoI) analysis will be the construction of a mathematical decision model that will synthesise the best available existing evidence from the literature and information from the pilot trial in order to provide preliminary estimates of effects, costs and cost-effectiveness. Uncertainty around estimates of effects, costs and cost-effectiveness will be accounted for by probabilistic sensitivity analysis and estimated using Monte Carlo simulation, as cost data are unlikely to be normally distributed. Statistical imprecision will be presented as confidence intervals around differences in effectiveness, costs and cost-effectiveness. Threshold sensitivity analyses will be applied to identify the range for costs and effects in which a treatment might need to exist in to be considered cost-effective with respect to standard thresholds for cost-effectiveness (e.g. £20,000 per QALY).

The VoI analysis will build upon the results of the probabilistic sensitivity analysis to estimate the expected value of sampling information (EVSI). The EVSI will quantify the value of reducing uncertainty via collection of additional data in a definitive trial. Comparing the value of additional information with the financial and opportunity cost to generate the additional information, the expected net gain (ENG) can be calculated as the difference between the EVSI and the total cost of conducting the further research. The optimal design of a definitive trial will maximise the ENG to society with regard to sample size. The optimal sample size is that which maximises the difference between EVSI and expected total cost of the research (both the direct cost of the research itself and the opportunity cost of delaying the implementation of a worthwhile intervention whilst research is ongoing). The estimated optimal sample size will be inflated according to the rate of missing data in the trial data to achieve the optimal sample size of complete data cases and to determine the final sample size for a definitive trial.

#### Qualitative analysis

Data transcription will be carried out verbatim. Transcripts will be anonymised by removing names of any individuals mentioned in the course of the interview; a participant key will be stored separately. Transcripts will be subject to thematic analysis [49]; analysis will be an iterative process, using the constant comparative method [50], derived from grounded theory. Qualitative software (NVIVO 10) will aid in the organisation of thematic codes and categories.

As described above, the qualitative process evaluation will provide rich data on the feasibility of the interventions and on the ‘mechanisms of change’ and the role of context. This will include data on fidelity (assessment of content and interaction), acceptability (LAC and practitioner perceptions about receiving and delivering the actual interventions) and the potential ‘mechanism of change’ (whether our theory of change pathways are borne out in practice) from both the perspective of the service provider and LAC (service user). These data will allow us to assess if either of the interventions is clearly more acceptable to both service users and providers, is more likely to be integrated into routine service delivery, and has greater potential to elicit behaviour change in the young person. The data collected within the qualitative interviews and focus group will be used to draw elements of the MET and SBNT interventions together into a single ‘optimised’ intervention if appropriate. This may occur if core components of each intervention are consistently reported as being acceptable to LAC and practitioners and can be combined together in a complementary way whilst retaining the essence of each approach.

Qualitative and quantitative data will be collected simultaneously, and both sources of data will be analysed separately; however, the data from different methods will be triangulated to ‘consider where findings from each method agree (convergence), offer complementary information on the same issue (complementarity) or appear to contradict each other (discrepancy or dissonance)’ [51].

## Discussion

This is the first UK-based randomised controlled trial that will assess the feasibility of delivering behaviour change interventions to decrease drug and alcohol use and support the mental health of looked after children in the UK. Previous cross-sectional research has highlighted the high prevalence rates of substance use and mental health difficulties within the LAC population. However, there is little intervention-based research outlining the most effective interventions to be used with this high-risk group of young people. It is necessary to conduct a feasibility study prior to a larger definitive randomised controlled trial where there are significant uncertainties regarding interventions and/or trial processes [52, 53].

The study will examine the feasibility of recruiting LAC (who score ≥2 on the CRAFFT) into the trial. In addition, the ability of trained and supervised drug and alcohol practitioners to deliver the randomised intervention to acceptable levels of fidelity will be assessed. The study will also examine the feasibility of the research team retaining participants in the trial for the follow-up data collection at 12 months.

NICE guidelines (UK) recommend multiple sessions of motivational interviewing or family-based support or group-based behavioural therapy over 1 to 2 years to reduce substance use in high-risk young people [17]. Due to the complexity and length of these interventions, they are not feasible to be delivered at scale. The current study will adapt and evaluate the pilot feasibility of two alternative evidence-based behaviour change interventions: Motivational Enhancement Therapy (MET)—a concentrated form of motivational interviewing [29]; Social Behaviour and Network Therapy (SBNT)—an approach drawing from family and social interventions in substance use [54]. Both interventions involve counselling but focus on different behaviour change pathways, with internal thoughts and views shaping the decisional balance in MET compared with external, social influences in SBNT. Whilst both of these interventions have been shown to be effective at reducing substance use, less is known about their effect with young people, particularly those who are looked after by the local authority and likely to have more fragmented family relationships.

For many LAC, it is the experience of abuse or neglect from within their families that has led them to local authority care, and this may be related to the high rates of psychiatric morbidity in this population [25]. The absence of a supportive family unit has been associated with increased rates of substance use in young people [55]. SBNT has been designed to mobilise and develop support networks which are wider than just biological family and include peers; it has been found to be effective in reducing substance use in adults when delivered through routine services. Whilst interventions based on SBNT have the potential to address this central vulnerability within a LAC population, the ability to identify a suitable social support network for a LAC is undetermined. Further, the acceptability and feasibility of both MET and SBNT must be examined.

The views of social workers, drug and alcohol practitioners and LAC will be essential to understanding the acceptability of a randomised trial of behaviour change interventions for substance using LAC. These data will also inform how best to identify and intervene to reduce substance use in this vulnerable population. Thus, we will assess whether attitudinal support and appropriate processes are evident for a future definitive trial. If feasibility and acceptability is shown, the findings of this trial will be used to inform a protocol for a definitive randomised controlled trial of behaviour change interventions to reduce risky substance use in young people aged 12–20 years who are looked after by the local authority.

